#### Phase 1 (months 0–6): group-based interventions

Participants allocated to interventions will attend eight 1-h group sessions online via Zoom over a 6-month period according to a prescribed ideal delivery schedule. Participants will be asked to provide approval these sessions to be recorded (so that they may provide data for analysis regarding intervention delivery, as described above). The facilitators running the interventions will have formal qualifications in CBT and will receive specialised training from experts in mindfulness training and setting realistic goals.

To ensure that all participants are encouraged to access the current best practice approach to smoking cessation, the Royal Australian College of General Practitioner’s [65] “Ask, Advise, Help'” model for smoking cessation will be offered to all participants from baseline, including active control group participants. This approach involves referral to behavioural counselling and provision of information on accessing Nicotine Replacement Therapy and stop-smoking medications where indicated. The behavioural counselling offered in the current study is via the Quitline service.

##### Arm 1

MiCBT is a four-stage therapeutic approach. [66] Therapy begins at the personal stage, with the internal promotion of experiential awareness and acceptance. The second stage introduces imaginary and in vivo exposure procedures, and the third stage extends mindfulness principles into interpersonal interactions. Stage four, the empathetic stage, involves developing ethical awareness and compassion, which is intended to help prevent relapse through counterconditioning. The approach is based on *Vipassana* (insight training) and the co-emergence model of reinforcement. This model proposes that operant behaviour is reinforced by the interoceptive feedback (i.e., conscious or unconscious bodily sensation) which co-emerges with self-referential cognitions, rather than the environmental consequences posited by Skinner. [67] Participants undergoing MiCBT will also be asked to complete 30—60 min of homework daily, including mindfulness practice twice daily and some readings. Homework will be guided by a smartphone application.

##### Arm 2

Participants allocated to the MT arm will learn mindfulness techniques and apply them to change their behaviour. The core concepts will be extracted from the MiCBT intervention, e.g., mindfulness of breath, body-scanning methods, and loving-kindness meditation. However, MT will exclude aspects of CBT which do not directly relate to the meditations. For instance, the first session of MiCBT will focus on attention regulation and weakening peripheral addictions, whereas the equivalent mindfulness training session will only address attention regulation. Participants allocated to this arm will also be asked to perform mindfulness practice twice daily (30–60 min) and access readings through the smartphone application.

##### Arm 3

Participants allocated to arm three will undergo the SRG intervention based on the Problems and Goals Assessment outlined by the Flinders Program. [68] The significant elements of this intervention are problem identification, planning for goal setting, SMART goal setting (specific, measurable, attainable, realistic, time-bound), and reviewing progress. Participants will collaborate to plan goals that may or may not directly pertain to smoking behaviour.

#### Phase 2: peer mentoring

After completing 6 months of group sessions, participants allocated to the three interventions will receive a further 6 months of peer support from a mentor who has achieved smoking cessation in the past. Peers will engage with participants via online blog forums for each intervention. Participants will be encouraged to share their experience with others who underwent the same intervention. These online communities will grow as more users are added upon completion of the group sessions at the 6-month timepoint.

#### Phase 3: data collection only

During the third phase, participants will not receive any intervention from the study, though they might be engaging with other resources such as those provided via the ‘Ask, Advise, Help’ protocol referred to above. We will continue to collect data for a further 6 months after participants have completed the peer support phase. All quantitative data will be collected via online Qualtrics surveys. Links for each Qualtrics survey will be sent to participants by SMS to their mobile phone or by email where the participant requests it.

### Statistical analysis

#### Timepoints

All psychological and behavioural measures (internal resilience, external resilience, self-efficacy, motivation, stress, nicotine dependency, and goal achievement) will be measured before randomisation and then at 3 monthly intervals for the first 12 months (see Table 1; baseline goal assessment at 5 weeks). A final collection of data on these scales will occur at 18 months to test for maintenance of impacts. Equanimity will be measured at baseline, and then weeks 7, 13, 20, 52, and 78 after commencement of phase 1.

In addition to the primary outcome (cessation at 6-months), smoking cessation will be assessed at 4, 8, 12, 16, 20, 52, and 78 weeks to address hypotheses and to compare the trajectory of smoking cessation between groups.

#### Analyses

All analyses will use Stata (version 17.0 [69]). This will be undertaken blinded to the participants’ group allocation. Mixed-effects modelling will be used to assess the effect of the interventions on primary and secondary outcomes. This approach accounts for the correlation of the data from repeat measures over time and reduces bias caused by missing data at one or more time points for each participant. In addition, we will develop prediction models to determine whether levels of internal and external resilience measured at baseline predict smoking cessation. As an exploratory analysis, we will also perform mediation analyses to determine the direct and indirect effects of the separate components of each intervention on the primary and secondary outcomes.

For outcomes assessed at a single time-point, we will assess the difference between the four groups at that time. For outcomes assessed at repeat time points, we will assess differences between the four groups at each time point, with adjustment for multiple comparisons. We will assess binary outcomes using mixed-effects logistic regression and continuous outcomes using linear mixed-effects regression. In repeated measures, we will treat time as a categorical variable, and the model will include fixed-effects for time and group. Subgroup analysis will be undertaken to test whether people with a critical level of resilience are more likely to stay quit than those that do not meet this level. The main analyses will be performed on a per-protocol basis. Our intention-to-treat population will be defined as all participants that were randomised and also completed the baseline survey. We will perform a sensitivity analysis on a modified intention-to-treat basis and impute missing data where possible. Where more than 10% of data are missing, we will also perform multiple imputation as a sensitivity analysis to account for possible bias in estimates caused by missing data. Missing smoking data will be presumed MNAR and analysed as continued smoking. Hypothesis testing will be performed using 2-tailed tests with a Type 1 error rate of alpha = 0.05, and 0.05/3 = 0.0167 when assessing each outcome across time to account for the repeated testing at 6, 12, and 18 months. We will make further adjustments for multiple comparisons (e.g., 3 comparisons with control) depending on each outcome.

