## Methods

The following protocol (version 5, September 9th 2022) follows SPIRIT guidelines for reporting protocols (see Additional file 1). In this four-arm parallel-group RCT of SRG, MT and MiCBT versus an active control (equal allocation ratio), we will deliver the interventions to small groups of smokers to maximise the potential cost-effectiveness. 6-months of these interventions will be followed by 6-months of online peer support and a further 6-month follow-up period. The control group will be directed to optional resources including counselling (Quitline) and information about pharmacological aid. We aim to: (a) test the efficacy of the three interventions (SRG, MT and MiCBT) for smoking cessation and (b) levels of resilience in low SES groups and how this changes during exposure to the interventions, (c) measure the cost-effectiveness and cost-utility of the interventions in low SES groups, and (d) undertake a process evaluation of the different interventions in low SES groups. We hypothesise the following:H1: The proportion of participants who report 14-day period abstinence from smoking at 6 months will be significantly higher for each intervention group compared to the control group.H2: Amongst participants that report 14-day period abstinence at 6 months, the proportion of participants who report 14-day period abstinence at 12 months will be significantly higher for each intervention group compared to the control group.H3: The proportion of participants who report 14-day period prevalence abstinence from smoking at 6 months post-trial (18 months from baseline) will be significantly higher for each intervention group compared to the control group.H4: Levels of resilience measured by the Connor-Davidson CD-25 [43] and ENRICHD Social Support Inventory [44] will be significantly higher for each intervention group compared to the control group at 6, 12 and 18 months post randomisation.H5: The interventions will improve smoking cessation and QALYs at a reasonable and acceptable incremental cost.

In addition, we pose the following research questions for the qualitative component of the study (that pertains to the process evaluation):RQ1: Have the different interventions been implemented and received as intended?RQ2: What are the barriers and facilitators associated with the first research question?RQ3: For whom, and in what circumstance were the interventions effective (and cost-effective) or not, and why?

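### The fixed effects named for the repeated-measures model (time and group) cannot give the group differences at 6, 12 and 18 months that the same section promises

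*Protocol article*

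**What the plan says.** All statements are in the protocol article.

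- **Target for repeated outcomes (Analyses):** "we will assess differences between the four groups at each time point, with adjustment for multiple comparisons". The same paragraph sets alpha at 0.05/3 = 0.0167 for the tests at 6, 12 and 18 months.
- **Model family (Analyses):** "We will assess binary outcomes using mixed-effects logistic regression and continuous outcomes using linear mixed-effects regression".
- **Fixed effects (Analyses):** "In repeated measures, we will treat time as a categorical variable, and the model will include fixed-effects for time and group". No interaction is named here or elsewhere.
- **Outcomes measured once (Analyses):** "For outcomes assessed at a single time-point, we will assess the difference between the four groups at that time".
- **H4 (Methods):** resilience "will be significantly higher for each intervention group compared to the control group at 6, 12 and 18 months post randomisation".
- **Cessation over time (Timepoints):** besides 6 months, "smoking cessation will be assessed at 4, 8, 12, 16, 20, 52, and 78 weeks", partly "to compare the trajectory of smoking cessation between groups". The 18-month scale data are meant to show whether effects last.

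**The concern.** A model with main effects of time and group assumes that each arm differs from control by the same amount at every visit. It has no parameter for a difference specific to 6, 12 or 18 months. The listed terms therefore conflict with the target stated in the same paragraph.

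An analyst who fitted exactly those terms would have one contrast per arm to report for all three times. If the effect builds up during the group sessions and fades later, that contrast understates the peak, overstates the late effect and hides the fade. The 0.0167 rule would have nothing to act on, because there would be no separate tests at the three times.

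**Working it through.** **1. The plan's own figure.** The sample size (Sample size and power analysis) is a comparison of two proportions at one time: 13.6% against 25.2%, two-sided alpha 0.05, power 80%.

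n = [1.960·√(2·p̄·(1−p̄)) + 0.842·√(p₁q₁ + p₂q₂)]² / (p₂ − p₁)²

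With p̄ = 0.194, this is [1.960·√0.3127 + 0.842·√0.3060]² / 0.116² = 2.439 / 0.01346 = 181.2, so 182 per arm. Then 182/0.90 = 202.2, so 203, and 4 × 203 = 812. All three figures reproduce. None depends on the terms of the repeated-measures model.

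**2. What the named terms can estimate.** The scales are measured at months 0, 3, 6, 9, 12 and 18 in four arms, which gives 4 × 6 = 24 cell means.

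| Fixed effects | Parameters | Arm-versus-control contrasts |
|---|---|---|
| time + group | 1 + 5 + 3 = 9 | 3 in total, the same at every visit |
| time + group + group-by-time | 24 | 3 at each visit |

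A check of the design-matrix ranks gave 9 and 24.

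**3. What the common contrast equals.** With complete data and a random intercept (both assumed here), the group coefficient is the simple average of the visit-specific differences. The documents give no effect profile, so the one used here is assumed: 0.2, 0.4, 0.3, 0.2 and 0.1 SD at months 3, 6, 9, 12 and 18.

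- Baseline not an outcome row: (0.2 + 0.4 + 0.3 + 0.2 + 0.1)/5 = 1.2/5 = 0.24.
- Baseline an outcome row with true difference 0: 1.2/6 = 0.20.
- True values: 0.40 at 6 months, 0.20 at 12 months and 0.10 at 18 months.

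**4. A second assumed profile.** Differences of 0.2, 0.5, 0.5, 0.4 and 0.2 SD at the same months average 1.8/5 = 0.36 without a baseline row and 1.8/6 = 0.30 with one. Fifteen simulated trials with 182 per arm and baseline as an outcome row gave a mean of 0.27 from time + group. With group-by-time they gave 0.46, 0.39 and 0.19 at 6, 12 and 18 months, where the true values were 0.5, 0.4 and 0.2.

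**5. Which hypotheses are touched.**

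| Hypothesis | Depends on the repeated model? |
|---|---|
| H1, abstinence at 6 months | Only if cessation is analysed in the repeated model |
| H2, abstinence at 12 months among those abstinent at 6 | No; one time, in a subset |
| H3, abstinence at 18 months | If taken from the repeated model |
| H4, resilience at 6, 12 and 18 months | Yes |

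For H1 the text points both ways. Mixed models are assigned to primary and secondary outcomes, and cessation is assessed at eight times. Yet the primary outcome is fixed at 6 months, cotinine is measured only then, and a separate rule covers outcomes assessed once.

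**The case against.** The best reply is that saying a model will include two terms does not say that it contains nothing else. The sentence is not a full specification: it names no random effect, although the models are called mixed. The promise of differences at each visit and the 0.0167 rule make sense only with time-specific contrasts, so the authors probably intended the interaction. A condensed article may also leave the full list of terms to an analysis plan.

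Much of this stands. A reader might infer that the plan rules the interaction out; the wording does not support that. It remains an internal inconsistency, because the article does state fixed effects, and those it states do not yield the analysis it describes.

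Three other stronger readings also go too far:

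- **That H1 to H4 all fail.** H2 does not use this model, and H1 can be met under the single-time-point rule.
- **That baseline necessarily dilutes the effect.** The article says that the scales are measured before randomisation, but not whether baseline is an outcome row or a covariate. A constant 0.30 SD effect would be estimated as 5 × 0.30/6 = 0.25 with a baseline row, but as 0.30 without one.
- **That the size of the distortion is known.** It depends entirely on the true profile over time. If the effect is constant after baseline and baseline is not a response, there is no distortion.

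For cessation, a 6-month risk difference can be computed from a main-effects logistic model. It would still be driven by an odds ratio held constant over all visits, so it is not a 6-month effect.

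**Conclusion.** The point holds as an inconsistency between the stated target and the named model terms. It falls firmly on H4 and on the trajectory and maintenance comparisons, on H3 if that comes from the repeated model, and on H1 only conditionally. The sample size stands.

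Under the first assumed profile, one value of 0.24 SD (0.20 with a baseline row) would stand in for 0.40 at 6 months and 0.10 at 18 months. That is 60% (or 50%) of the 6-month effect and 2.4 (or 2.0) times the 18-month effect. These sizes are illustrative. That the named terms give a single common contrast follows from the model itself and needs no assumption about effects.

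**What to change.** - Change the model sentence to name fixed effects for time, group and group-by-time.
- State that the arm-versus-control contrasts at 6, 12 and 18 months are taken from that model, and that H1 is the 6-month contrast.
- For the scales, enter the baseline score as a covariate or constrain the arm means to be equal at baseline.

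The cost is a few words and some degrees of freedom: at most 24 − 9 = 15 more fixed effects for a scale measured at six times, which is small against 812 participants. No new data are needed.

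A separate, optional improvement, which corrects no error in the plan, is to adjust the smoking models for baseline variables already collected, such as nicotine dependence.

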#### Costs-effectiveness

Any intervention effects on smoking cessation were not anticipated to lead to differences in health care use (e.g., GP visits, hospitalisations, etc.) between the control and intervention groups over the time horizon of the clinical trial. The lack of an expected effect on health care use did not justify the additional burden of collecting resource use and cost data from participants.

A trial-based economic evaluation will estimate intervention costs, in total, per intervention group participant, per additional intervention group participant demonstrating smoking cessation and per mean change on the EQ5D-5L quality of life instrument. If significant differences in smoking cessation rates are observed, external data describing the long-term health benefits and health care cost impacts will be sought to inform modelled estimates of downstream cost, mortality, and quality of life effects. These data will inform the estimation of the incremental cost per QALY gained.

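### The outcome model as described names time and group but no baseline covariate, so it forgoes precision on the resilience scales, and no step returns the smoking result to the proportion scale of H1

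*Protocol article*

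**What the plan says.** The Analyses section of the protocol article sets the model type: "We will assess binary outcomes using mixed-effects logistic regression and continuous outcomes using linear mixed-effects regression". For repeated measures, with time taken as categorical, it then names the terms: "the model will include fixed-effects for time and group". Neither sentence mentions a baseline covariate or an effect measure such as a risk difference.

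The Timepoints section says that the psychological and behavioural scales "will be measured before randomisation and then at 3 monthly intervals for the first 12 months", with a last collection at 18 months. The first goal assessment is the exception, at week 5. Baseline resilience does have a stated use, but in a separate exercise: "we will develop prediction models to determine whether levels of internal and external resilience measured at baseline predict smoking cessation".

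H1 is worded on the proportion scale: "The proportion of participants who report 14-day period abstinence from smoking at 6 months will be significantly higher for each intervention group". The sample size section uses the same scale, 25.2% against 13.6%. Beyond the 6-month primary time point, "smoking cessation will be assessed at 4, 8, 12, 16, 20, 52, and 78 weeks".

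**The concern.** In a randomised trial, a participant's own baseline score is usually the best predictor of the later score on the same scale. Conditioning on it narrows the interval for the group effect at no extra data cost. H4 rests on two such scales at 6, 12 and 18 months, and both are collected before randomisation. If the model is fitted with the named terms and nothing else, that information is either unused or, if baseline is entered as one more time level, used in a way that pulls the group effect towards zero.

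For smoking, the available prognostic factors are dependence, motivation and self-efficacy. The issue of scale is separate. A logistic model with a participant random effect returns a participant-specific odds ratio, while H1 and the sample size are stated as proportions. No step from one to the other is described, so a reader could set the reported odds ratio against the planned effect and misjudge it.

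**Working it through.** **1. The plan's own figure.** Inputs from the sample size section: 25.2% and 13.6%, two-sided alpha 0.05, power 80%. With pooled variance and no continuity correction:

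n = [1.96·√(2·0.194·0.806) + 0.842·√(0.136·0.864 + 0.252·0.748)]² / 0.116² = (1.096 + 0.466)² / 0.01346 ≈ 181.2, rounded up to **182**.

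Then 182/0.9 gives 203 per arm, and 4 × 203 = 812. Power at 182 per arm is 80.2%. The stated figures reproduce from an unadjusted comparison.

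**2. Scale outcomes, baseline left out or conditioned on.** The detectable standardised difference from follow-up scores alone is 2.80·√(2/182) = 0.294 SD. Conditioning on baseline multiplies this by √(1 − ρ²), where ρ is the baseline/follow-up correlation. The article gives no ρ for this population and interval, so a range is assumed.

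| ρ (assumed) | Variance factor 1 − ρ² | Detectable difference |
|---|---|---|
| baseline not used | 1 | 0.294 SD |
| 0.3 | 0.91 | 0.280 SD |
| 0.5 | 0.75 | 0.254 SD |
| 0.7 | 0.51 | 0.210 SD |

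Alpha here is 0.05. A stricter alpha raises every row by the same proportion.

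**3. Scale outcomes, baseline entered as a time level.** The visits are at 0, 3, 6, 9, 12 and 18 months, six in all. Take main effects for time and group, a random intercept and complete data. The group coefficient is then the difference in means averaged over all six visits. If the true effect is 0 at baseline and δ at each of the five later visits, its expectation is (0 + 5δ)/6 = 0.83δ, a dilution of 1/6.

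**4. Smoking at 6 months, prognostic adjustment.** Effective n is approximated as 182/(1 − R²), with R² assumed.

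| R² (assumed) | Effective n per arm | Power at alpha 0.05 |
|---|---|---|
| 0 | 182 | 80.2% |
| 0.02 | 186 | 81.0% |
| 0.05 | 192 | 82.2% |
| 0.10 | 202 | 84.1% |

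**5. Scale of the smoking effect.** From 25.2% and 13.6%:

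- risk difference: 11.6 points
- risk ratio: 0.252/0.136 = 1.85
- marginal odds ratio: (0.252/0.748)/(0.136/0.864) = 2.14

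For a random-intercept logistic model, the two intercepts were solved so that the average over the random effect gives exactly these proportions. The conditional odds ratio is then 2.20, 2.40 and 3.17 at random-intercept SDs of 0.5, 1 and 2, and 3.41 at a latent intraclass correlation of 0.6. These variances are assumed; the article gives none. In each SD case, averaging back over the random effect returned 11.6 points.

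**6. How the two remedies interact.** In 2,000 simulated trials with a covariate of odds ratio 2.7 per SD, adjustment raised power from 81% to 86% and moved the odds ratio from 2.17 to 2.44. Adjustment helps the test but takes the odds ratio further from the marginal 2.14. An adjusted model therefore needs a standardised risk difference reported with it.

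**The case against.** The strongest reply is that this is a condensed article. It says what the model will include, not that nothing else enters, and covariate lists and effect measures are commonly left to an analysis plan that is not shown. That stands as far as it goes: the text does not say that the terms are limited to time and group. But the article does name model terms, and it places baseline resilience in separate prediction models. It is fair to say that a better specification than the one described is available.

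Four stronger readings are tempting, and the document supports none of them.

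- *Planned power is lost.* It is not. The 80% was computed unadjusted and reproduces. Unstratified randomisation also leaves the unadjusted test valid, because its standard error already allows for chance imbalance.
- *The model overstates the effect.* A conditional odds ratio of 2.7 and a marginal one of 2.14 can describe the same two proportions. The article does not say that an odds ratio will be the headline result. It also has a separate rule for outcomes assessed at a single time point. If 6-month cessation falls under that rule, there may be no participant random effect; the repeated cessation assessments leave this open.
- *The baseline of the outcome itself is ignored for smoking.* Every participant smokes at entry, so there is no varying baseline to use, only prognostic covariates.
- *Cost per additional quitter cannot be obtained.* The economic section asks for cost "per additional intervention group participant demonstrating smoking cessation" but does not tie it to the regression. Arm-level counts suffice, and missing smoking data are counted as smoking.

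Two cautions on the inputs also stand. The 0.87 quoted for the CD-25 is test-retest reliability in a clinical sample and is no guide to a 6- to 18-month correlation here. Entry is limited to people planning to quit, which may narrow the spread of motivation and favour the lower R² values.

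Baseline may indeed enter as a time level. That does not rescue the named terms, as step 3 shows. The article does promise group differences at each time point, which needs group-by-time terms that it does not name. With those terms added and baseline means left free, the contrast at a follow-up visit with complete data is the raw difference in means at that visit, so baseline still adds nothing to it.

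**Conclusion.** The point holds as a recommended improvement, not as an error that undermines the trial. It matters most for the H4 scales: the detectable difference would fall from 0.29 SD to 0.25-0.21 SD if ρ is 0.5-0.7, and only to 0.28 SD if ρ is 0.3. The alternative of baseline as a time level under main effects carries a dilution of about one sixth, given six complete visits, a random intercept and a constant effect after baseline.

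For 6-month smoking the gain is about 1 to 4 points of power at R² 0.02-0.10, on top of a planned 80% that is already met. The effect-measure point is conditional. If the mixed-effects logistic model is used, its odds ratio (about 2.2 to 3.4 over the assumed random-intercept variances) is not comparable with the marginal 2.14 implied by the sizing assumptions. ρ, R² and the random-intercept variance are assumptions throughout; the article supplies none of them.

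**What to change.** 1. For each scale measured before randomisation in all arms (both resilience scales, self-efficacy, motivation, stress, dependence), state that the model adjusts for the participant's own baseline value. Use an ANCOVA-type mixed model, or a constrained longitudinal model with a common baseline mean, and in either case group effects by time.
2. For 6-month smoking, state a short covariate list: baseline Fagerstrom score, Contemplation Ladder and self-efficacy.
3. From that smoking model, report the standardised 6-month risk difference with 95% CI for each intervention arm against control, alongside the odds ratio.

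The cost is wording in the analysis plan; the data are already collected. The one constraint is that the covariates must be fixed before unblinding.

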#### Secondary outcomes—investigating the mechanisms influencing behaviour change

##### Internal and external resilience

The 25-item Connor-Davidson CD-25 scale measures the internal resilience construct of the psychosocial model of resilience. [43] Connor and Davidson [43] found evidence for the convergent validity of the scale and observed satisfactory internal consistency (α = 0.89) in the general population and satisfactory test–retest reliability (intraclass coefficient = 0.87) in a clinical sample.

The 7-item ENRICHD Social Support Inventory [44] will be used to measure self-reported external resilience. Mitchell [44] found evidence of convergent validity and observed satisfactory internal consistency (⍺ = 0.86). Vaglio et al. [49] observed satisfactory test–retest reliability over a one-month interval (intraclass correlation = 0.94).

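### The planned resilience subgroup analysis splits graded scale scores at a threshold, which loses information, and its contrast is prognostic rather than a test of who benefits

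*Protocol article*

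**What the plan says.** The subgroup analysis is described in one sentence of the Analyses section of the protocol article: "Subgroup analysis will be undertaken to test whether people with a critical level of resilience are more likely to stay quit". The sentence fixes two things: the comparison has two levels, and it sets people who reach the threshold against everyone below it.

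Resilience itself is graded. Under Internal and external resilience, the article states: "The 25-item Connor-Davidson CD-25 scale measures the internal resilience construct of the psychosocial model of resilience". It also states: "The 7-item ENRICHD Social Support Inventory [44] will be used to measure self-reported external resilience". According to Timepoints, both scales "will be measured before randomisation and then at 3 monthly intervals for the first 12 months", with a final measurement at 18 months.

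Other planned work bears on the point:

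- Analyses also says: "we will develop prediction models to determine whether levels of internal and external resilience measured at baseline predict smoking cessation". No split is mentioned there.
- For the repeated-measures models, "the model will include fixed-effects for time and group". No resilience-by-group term is described.
- Methods lists, as RQ3 of the qualitative component: "For whom, and in what circumstance were the interventions effective (and cost-effective) or not, and why".

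**The concern.** Two features of the stated analysis are weak whatever threshold is eventually used.

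First, splitting a graded score treats everyone on the same side of the line as alike. People just above and just below it count as different, while people far apart on one side count as equal. Unless the true relation is a step at exactly that level, information is lost.

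Second, a subgroup analysis in a randomised trial normally asks whether the treatment effect differs between subgroups. This one compares more resilient with less resilient people, and treatment arm does not enter the comparison. A positive result would show that resilient people do better, not that they gain more from the interventions. Resilience is the trial's organising idea, so a result carrying the subgroup label could easily be misread.

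**Working it through.** **The plan's own figures.** The article gives no figure for the subgroup analysis, so its sample size was checked first. Inputs from Sample size and power analysis: 13.6% versus 25.2% abstinent, two-sided alpha 0.05, 80% power, 10% drop-out.

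- Pooled-variance formula, mean proportion 0.194: n = [1.96 × √(2 × 0.194 × 0.806) + 0.8416 × √(0.136 × 0.864 + 0.252 × 0.748)]² / 0.116² = 181.2, rounded up to 182 per group.
- 182 / 0.90 = 202.2, rounded up to 203; 4 × 203 = 812.

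Both stated figures reproduce.

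**How many people can stay quit.** H2 concerns abstinence at 12 months among those abstinent at 6 months. On that reading, with all three active arms at 25.2% (the article uses this rate for mindfulness training only):

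- 182 × (3 × 0.252 + 0.136) = 182 × 0.892 = 162;
- with 203 per arm, 203 × 0.892 = 181.

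**Information kept by a split.** For a normal score with a fraction q above the cut c, relative efficiency is φ(c)² / [q(1 − q)].

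| Cut | q | Information kept |
|---|---|---|
| Median | 0.50 | 0.637 |
| Top quartile | 0.25 | 0.539 |
| Top tenth | 0.10 | 0.342 |

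Applied to 162 quitters, a median split is worth about 0.637 × 162 = 103 people analysed on the full score, and a quartile split about 0.539 × 162 = 87.

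**Effect on power.** This was simulated with 10,000 runs, 162 people, a standard normal score, 50% staying quit and a log-odds relation linear in the score. The 50% and the effect sizes are assumptions.

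| Log odds ratio per SD | Continuous | Median split | Top-quartile split |
|---|---|---|---|
| 0.35 | 58% | 40% | 37% |
| 0.47 | 82% | 63% | 57% |

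**If the cut were chosen from the same data.** With no true association, the same 162 people and 50% staying quit, the false-positive rate at nominal 5% is:

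- one preset cut, or the continuous score: about 5%;
- best of three quartile cuts: about 13%;
- best of 17 cuts from the 10th to the 90th percentile: about 30%;
- every possible cut in that range: about 44%.

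**Power of an interaction test.** Take one active arm against control, 182 per arm split into equal halves of 91, with an 11.6-point effect in one half and none in the other.

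- Variance in the half with an effect: (0.1175 + 0.1885) / 91 = 0.00336.
- Variance in the half without: (2 × 0.1175) / 91 = 0.00258.
- Standard error: √0.00594 = 0.0771.
- Power: Φ(0.116 / 0.0771 − 1.96) = Φ(−0.46) = about 32%.

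For 80% power, the effect would have to differ between halves by about 2.80 × √(2 × 0.00336) = 0.23, or 23 percentage points.

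**The case against.** Much can be said for the plan.

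- **The missing threshold.** A reader might fault the article for not naming the level, the scale or the measurement time. These details commonly sit in an analysis plan, which is not shown here, so their absence is not part of this point.
- **A searched-for cut.** A reader might infer that the level will be picked from the trial data. The text does not say so, and a level that people meet reads at least as naturally as one set beforehand. The inflated error rates above are conditional, and 44% is the extreme case.
- **A broken promise on effect modification.** The sentence asks only whether people at the level do better. None of H1 to H5 concerns modification by resilience, and RQ3 belongs to the qualitative component. The fault is the label and what it invites, not a failed commitment.
- **Restriction to quitters.** The sentence refers to people and does not define staying quit. Restriction to six-month quitters is a plausible reading taken from H2, but the documents do not state it.
- **A true threshold.** If abstinence really changed in a step at a known level, a split there would lose little. That can be checked by modelling the score flexibly, but a split assumes it.
- **Work already planned.** The baseline prediction models may use the full scores, which offsets part of the loss for cessation. They do not replace the comparison of who stays quit, and they too are prognostic.

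What remains is the stated dichotomy and a label that does not match the contrast.

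**Conclusion.** The point holds, as a minor one. The article commits to a two-level comparison of graded scores, which keeps about 64% of the information at a median split and 54% at a quartile split. These figures assume a normal score and a smooth association; the base of about 162 further assumes the H2 reading and the 25.2% rate in all three active arms. The comparison describes prognosis and cannot support a statement about who benefits from the interventions. The documents do not support the stronger conclusions that error rates will be inflated or that a planned effect-modification test is faulty. The analysis is secondary, and neither the primary comparison nor the sample size is affected.

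**What to change.** - Replace the two-level comparison with baseline CD-25 and ENRICHD scores as continuous terms in the smoking-abstinence models, with a spline to check for a threshold, and show the fitted curve. This fits the prediction models already planned.
- Describe this analysis as prognostic, and label any association restricted to quitters as descriptive.
- If a claim about who benefits is wanted, add an arm-by-baseline-resilience interaction in all randomised participants. Label it exploratory and report estimates with confidence intervals, since its power is low.
- If a threshold is still to be reported, justify it in writing before the outcome data are examined.

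The cost is analysis-plan wording only: no new data, participants or software.
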